## Randomization

The children aged 4–6 years within four classes (two classes selected from K2 and K3 grade, separately) will be randomized from the designated kindergartens using Research Randomizer software. The preschoolers in each class who meet the eligibility criteria will be screened by the kindergarten teachers and staff. To avoid changes in teachers and classmates affecting the results of this course, we will intervene in the form of a nature class. In total, 12 nature classes in grades K2 and K3 from the 3 kindergartens will be assigned to a PE curriculum in their respective schools, that is, 4 classes in the sport-featured kindergarten with “Hello sunshine” PE curriculum, the OPE group will have ordinary PE classes, the PE class in the FP group will be free play. This sequence will then be concealed in an opaque envelope.

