### Interventions

In the study, the participants will be divided into three groups. The PE teacher will use various kinds of ball game-based curriculum in the HS group. The OPE group will have the ordinary preschool PE class that uses the kindergarten-based syllabus with a PE teacher (ball skills are not the main teaching contents). The FP group will play freely in outdoor activities with no guidance from teacher. The three groups will have the same daily life at kindergarten, except for the content of the PE class and outdoor time. PE classes will be 25 or 30 min, one or two times per week (depending on the student grade). Outdoor time will be implemented for 30 min per day, 5 days a week for 10 weeks during the intervention period. All three methods (HS, PE, and FP) are believed to improve motor skills and physical activity. The differences in the three methods are described below. This description follows the Template for Intervention Description and Replication checklist and guidelines for better reporting of interventions (Hoffmann *et al.*, 2014).

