#### HS group

The HS project’s design is based on the physical literacy framework (Whitehead, 2013). It is a well-structured, age-demarcated, PE curriculum that includes five modules: knowledge, motor skills, physical quality, psychological quality, and health behavior. Each module has different course objectives and content in accordance with age. The HS curriculum consists mainly of ball skills activities including teaching or practicing ball skills in PE class, ball club time, and autonomous regional area in outdoor time. It consists of nine kinds of ball activities, such as football, basketball, badminton, table tennis, baseball, golf, handball, bowling, and snooker. K2 students will have a PE class (one ball topic for 25 min) and a ball clubs’ class (children volunteer to join any club for 60 min) once a week. In addition, they will have one football activity (autonomous regional play) in the afternoon outdoor time, daily. K3 children will have PE class (football or basketball) twice a week and ball club activities once a week, and football topic activity two times and golf topic activity in outdoor activity time once. In the PE class, ball game-related general knowledge, ball skills, and so on will be taught. In ball clubs’ time, children will participate and practice in ball games with the PE teacher. During outdoor activity, children will play in an autonomous regional ball area with supervision by the vice-class teacher for 30min.

An experienced PE teacher will teach basic ball skills in the context of a game or story and motivate the children to complete the task, while also enjoying themselves. The teacher will guide the children through the preset game scenarios, while demonstrating and explaining basic ball skills and their task or activity execution via prompt words that remain consistent with the teaching plan. Timely encouragement and feedback will also be provided to the children. During the outdoor class, high-autonomy interventions, wherein the children have the freedom to self-navigate through a ball skills game station are to be conducted.

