### Covariate and mediator

#### Personal factors

Age will be calculated as the children’s month-based ages, as it is going to affect the intervention’s outcome. Participants’ perceived motor competence will be measured with a pictorial scale for perceived movement skill competence (PMSC) that builds upon the TGMD-2 (Barnett *et al.*, 2015). It consists of 13 pictures illustrating cartoon boys (boy version) or girls (girl version) performing TGMD-3 skills. It shows middle to high instrument reliability and face validity in Chinese children (Diao *et al.*, 2018). Children will be shown illustrations by the examiner and judge whether the cartoon character is good at doing the skills, then choose between four Likert scale options (1 to 4, from “not too good” to “really good”).

Individual temperaments are expected to be predictive of the differential effects of this motor skills intervention (Taunton *et al.*, 2018), and they will be assessed using the 36-item Children’s Behavioral Questionnaire-Very Short Form (CBQ-VSF) (Putnam and Rothbart 2006). The test is divided into three broad dimensions: surgency, negative affect, and effortful control and it demonstrates acceptable internal consistency. It is a very short form based on the well-established parent report measure of temperament CBQ questionnaire for children aged 3 to 8 years (Rothbart *et al.*, 2001) and it has medium to high reliability and validity confirmed by studies in multiple countries. The CBQ-VSF provides moderate reliability of scale scores for assessing temperamental characteristics in preschoolers (de la Osa *et al.*, 2014).

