## Results

Data will be imported from Excel 2019 to IBM SPSS version 26.0 for inferential statistical analysis. The normal distribution of the data will be checked before determining the descriptive statistics for all variables (means and standard deviations). The participants’ basic information will be descriptive, including age, gender, and BMI. The primary outcomes will be expressed as continuous. If data are approximately normal distribution, the effect of the PE curriculum intervention on dependent variable (FMS, or TGMD, or HTKS, or SCEB score) will be investigated with repeated ANOVAs within factor: time (pre and post), between factors: group (HS, OPE, and FP) and gender (boy and female) and Bonferroni post hoc tests. Further, the relationship between FMS and other domains will be identified by regression analysis. Finally, the potential influence of individual factors (such as age, gender, and temperament) on the intervention effect will be investigated by comparing the gain in FMS score and subscale. Multiple regression equation is used to further explore the extent to which social-ecological factors contribute to the FMS score level at baseline. Statistical significance will be set at *P* < 0.05.

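### The model for the curriculum effect omits grade and age, although classes are selected by grade and the protocol expects age to matter; adding either is a cheap, modest improvement

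*Protocol article*

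**What the plan says.** - **Effect model (Results).** The effect of the PE curriculum on each dependent variable is to be tested by repeated ANOVA with "within factor: time (pre and post), between factors: group (HS, OPE, and FP) and gender (boy and female) and Bonferroni post hoc tests". No term for grade, age or class is listed.
- **Selection of classes (Randomization).** Within each designated kindergarten there are "two classes selected from K2 and K3 grade, separately", which makes up "12 nature classes in grades K2 and K3 from the 3 kindergartens". The arm itself is fixed by the kindergarten.
- **Age (Covariate and mediator, Personal factors).** "Age will be calculated as the children’s month-based ages, as it is going to affect the intervention’s outcome".
- **Later use of age (Results).** Age, gender and temperament are examined afterwards by comparing gains in the FMS score and subscale. HTKS, SCEB-30, physical fitness and anthropometrics, all primary in Table 1, are not part of that comparison.
- **Schedule by grade.** The Interventions section says in general: "PE classes will be 25 or 30 min, one or two times per week (depending on the student grade". The HS group section gives separate schedules: "K2 students will have a PE class (one ball topic for 25 min) and a ball clubs’ class" once a week, against two PE classes and one club session for K3. The OPE group section gives K2 and K3 the same frequency, five times a week. The FP group section states no difference by grade.

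**The concern.** Grade is the one characteristic of the children that the class selection holds balanced, and it is a close proxy for age, which the protocol itself expects to matter. The effect model uses neither, while it does include gender, which structured nothing in the design.

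A pre–post analysis removes differences between grades in level. It does not remove differences in gain, which could arise from maturation or from less room to improve on a bounded scale such as the HTKS (0 to 52). Two things follow if such a difference exists. It sits in the residual and makes the group × time test less precise than the design allows. And if the share of K3 children differs between arms, part of the grade difference is attributed to the curriculum.

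**Working it through.** **The plan's own figure.** 3 × 83 = 249 is confirmed. The effect size behind 83 is not stated. Working back with a two-sided 5% level (sidedness assumed) and 80% power, 79 per arm × 1.05 = 82.95, so 83, which corresponds to a detectable difference of (1.960 + 0.842) × √(2/79) = 0.446 SD. Dividing instead, 78 / 0.95 = 82.1, so 83, which corresponds to 0.45 SD. I use 79 evaluable children per arm and 0.446 SD as a reference point near 80% power, not as the sponsor's assumption.

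**Assumptions not in the document.** The K2–K3 difference in 10-week gain is g, in units of the within-grade SD of gain; 0.3 to 0.5 is taken as the working range. The grade mix is 50:50 in each arm, as two K2 and two K3 classes per kindergarten suggest.

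**Precision.** With two time points, the time × group test is a test of group on gains. Leaving grade out multiplies the residual variance of the gain by 1 + g²/4.

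| g | Variance factor | SE factor | Power at 0.446 SD, grade omitted | n per arm to restore 80% |
|---|---|---|---|---|
| 0.25 | 1.016 | 1.008 | 79.4% | 81 |
| 0.3 | 1.0225 | 1.011 | 79.1% | – |
| 0.5 | 1.0625 | 1.031 | 77.6% | 84 |
| 1.0 | 1.25 | 1.118 | 70.7% | 99 |

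The row for 0.3 follows from 2.802 / 1.011 − 1.960 = 0.81, so Φ(0.81) = 79.1%. With grade in the model, power stays at 80.0% throughout. The last row is a stress case outside the working range.

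**Check by simulation.** Three arms of 79, group × gender model on gains, 4,000 runs, equal grade mix, HS better by 0.446 SD. At g = 0.5 the power of the three-arm test was 80.0% without grade and 82.3% with it. Under the null the rejection rate was 4.3% without grade and 5.4% with it (Monte Carlo error about 0.3 points). With a balanced mix the omission therefore makes the test slightly conservative; it does not inflate false positives.

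**Bias if the mix differs.** Bias in an arm contrast = g × difference in K3 share. For a 10-point difference: 0.3 × 0.10 = 0.03 SD and 0.5 × 0.10 = 0.05 SD. As an illustration only, with K3 shares of 60/50/40% and g = 0.5 the simulated type I error was 6.7% without grade and 5.4% with it.

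**Does one grade term capture the schedule?** From the HS section, PE class plus club time per week is 25 + 60 = 85 minutes for K2 and 2 × 30 + 60 = 120 minutes for K3, if the K3 club session is also 60 minutes. The OPE section states no difference by grade. A difference present in one arm is a group × time × grade effect; a common time × grade term cannot represent it.

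**The case against.** The strongest case against is one of proportion. For the child-level ANOVA that the article plans, the loss is 1% to 3% of a standard error, and it rests on a grade gap that no section gives. Class clustering matters far more: with about 21 children per class (83 / 4) and an assumed intraclass correlation of 0.05, the design effect is 1 + 20 × 0.05 = 2, so the child-level standard error is about 29% too small. Adding grade does nothing for that, nor for having one kindergarten per arm. All of this stands, and it limits the point to a modest improvement.

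Four stronger readings are tempting, and the document does not support them.

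- **That the plan loses 10 or more points of power.** A class-level test of 12 class means (intraclass correlation 0.05, effect 0.6 SD) would fall from 68% to 58% at g = 0.3, or to 41% at g = 0.5, and its 95% CI half-width would widen from 0.49 to 0.55 or 0.66 SD. The article does not plan that test. These figures apply only if the analysis is changed to respect the intact classes.
- **That the arms have unequal grade mixes.** Two classes per grade in each kindergarten point to near balance. Class size, consent and dropout could disturb it, but nothing shows that they have.
- **That grade sets the PE dose in all arms.** Different K2 and K3 schedules are spelled out only for HS.
- **That grade must be adjusted for as a randomisation stratum.** It is a stratum for selecting classes, not for allocating treatment. The case for including it is precision and protection, not that rule.

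It may also be said that covariates belong in a statistical analysis plan. That would answer a model left open. Here the Results section lists the factors, and the list does not carry through what the section on personal factors announces.

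**Conclusion.** The point holds in a limited form. The stated effect model omits both grade and age, against the protocol's own class selection and its own expectation about age, and the later FMS comparison does not make good the omission for any primary outcome.

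Under an assumed K2–K3 gap in gain of 0.3 to 0.5 SD and a 50:50 mix, including grade makes the child-level standard error about 1% to 3% smaller, worth roughly 1 to 2.5 points of power near 80%. It also protects the contrast against 0.03 to 0.05 SD of bias per 10-point difference in K3 share, should one arise. If the true gap is near zero, nothing is gained and almost nothing lost. The omission does not by itself invalidate the planned comparison.

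**What to change.** - In the Results section, for every primary outcome, add grade (K2/K3) with time × grade to the model with time, group and gender. Age in months with its time interaction is an acceptable alternative.
- Report the group × time contrast at equal grade weights.
- Examine group × time × grade as exploratory, because the stated HS schedule differs by grade and the common term cannot show this.
- Reconcile the PE frequency in the Interventions section (once or twice a week by grade) with that in the OPE group section (five times a week in both grades). Also make the number of classes in Participants (two in K2–K3) agree with that in Randomization (four per kindergarten), since the balance by grade rests on it.

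The cost is a sentence or two in the article and one extra factor in SPSS. Grade is known for every child. On gains with 79 per arm, residual degrees of freedom go from 3 × 79 − 6 = 231 to 230; in a class-level analysis they would go from 9 to 8. Clustering by class and the confounding of arm with kindergarten need separate treatment.

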### Aim

This study aims to conduct a “Hello Sunshine” curriculum project and evaluate its effects on the development of physical, motor, cognitive, and social competence in preschoolers. It also aims to determine the social-ecological factors influencing the intervention’s effect.

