### Research questions

The following research questions are proposed in this study:What are the effects of the HS project interventions on the physical fitness and motor development of preschool children, as well as on their cognitive and social competencies?How do intervention effects differ among the HS group, the OPE group, and the FP group?To what extent are the intervention gains on the HS groups mediated by personal factors?What are the main social-ecological variables related to differences in the intervention outcomes?To what extent are the outcome variables related to each other?

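### The only stated regression on family and environment factors has baseline FMS as its outcome, so the question of what relates to differences in intervention outcome has no matching analysis at those levels

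*Protocol article*

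**What the plan says.** The Aim section sets a second aim beside the evaluation of the programme: "It also aims to determine the social-ecological factors influencing the intervention’s effect". Research question 4 asks: "What are the main social-ecological variables related to differences in the intervention outcomes". The Hypotheses section expects differential effects within the HS group to be associated with individual, family and environmental factors. Strengths and limitations says that the impact of social-ecological factors on the interventions' effects will be analysed.

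The Results section contains three relevant analyses.

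- The main model is a repeated-measures ANOVA with time (pre, post) as the within factor and "between factors: group (HS, OPE, and FP) and gender (boy and female) and Bonferroni post hoc tests".
- For the individual level, "the potential influence of individual factors (such as age, gender, and temperament" and so on) "on the intervention effect will be investigated by comparing the gain in FMS score and subscale".
- For social-ecological factors, "Multiple regression equation is used to further explore the extent to which social-ecological factors contribute to the FMS score level at baseline".

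Research question 3 concerns personal factors: "To what extent are the intervention gains on the HS groups mediated by personal factors".

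**The concern.** The regression named for social-ecological factors has an outcome that is fixed before any child receives the programme. It can show which homes and surroundings go with higher starting skill. It cannot show which go with a larger or smaller benefit. This is not a detail left to an analysis plan: the article names the dependent variable, and it does not fit the question.

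The parent questionnaire items under Family factors and Environment factors would then be collected without a stated analysis linking them to response. The article hopes to inform teaching methods from the factors that affect the intervention's results, so correlates of starting skill might be read as correlates of programme success.

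Two smaller matters go with this. The gain comparison for individual factors does not say whether it is made within HS or across groups, and the answer depends on that. Research question 3 also speaks of mediation, although an intervention cannot change age or gender, and the article treats temperament as a predictor of differential effects.

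**Working it through.** **Promise against plan.** No stated figure tests this point. The sample size (3 x 83 = 249) serves below only as the size of an illustration.

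| Level | Promised | Stated analysis | Match |
|---|---|---|---|
| Individual (age, gender, temperament) | Question 3, Hypotheses | Gain in FMS; gender also in the ANOVA | Partial |
| Family, environment | Aim, question 4, Hypotheses, Strengths and limitations | Regression on baseline FMS | None |

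Study procedure places baseline testing in the initial two weeks and repeats the assessment at the end of the 10-week intervention. The regression outcome is therefore a pre-intervention score.

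**What each analysis estimates.** Let x be a factor with SD 1. Let β be its link to the starting score, γ its link to ordinary growth in every group, and δ its modification of the HS effect. All values are assumed, in approximate SD units:

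- pre = βx + u + e1
- post = βx + u + 0.3 + γx + HS(0.4 + δx) + e2
- SD of u is 0.8; SD of e1 and e2 is 0.5
- gain = 0.3 + γx + HS(0.4 + δx) + e2 − e1

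The expected slopes on x are:

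- (a) baseline FMS on x: β, which contains no δ
- (b) gain on x within HS only: γ + δ
- (c) group x factor on gain, HS against the other two groups: (γ + δ) − γ = δ

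**Simulation**, 83 per group, 2000 runs per row, no class effect. Cells give the mean slope and the share of runs with P < 0.05.

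| β, γ, δ | (a) baseline | (b) HS-only gain | (c) group x factor |
|---|---|---|---|
| 0.5, 0, 0 | 0.499, 100% | −0.002, 5.1% | −0.001, 5.2% |
| 0.5, 0, 0.3 | 0.499, 100% | 0.300, 96.0% | 0.298, 86.8% |
| 0, 0, 0.3 | 0.000, 6.0% | 0.300, 96.2% | 0.302, 87.6% |
| 0.5, 0.2, 0 | 0.497, 100% | 0.202, 72.8% | 0.001, 4.4% |

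Rows 1 and 2 differ only in δ, and the baseline regression cannot tell them apart. In row 3 a true modifier is found at little more than the 5% error rate. Row 4 bears on the gain comparison. With equal factor-driven growth in all groups and no modification, a comparison confined to HS is significant in 73% of runs, while the group contrast stays near 5%. The Hypotheses section does expect improvement in all groups.

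**Price of the contrast.** The gain residual variance is 0.5² + 0.5² = 0.5.

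- SE of the HS slope: √(0.5/83) = 0.078
- SE of the slope in the other two groups: √(0.5/166) = 0.055
- SE of the interaction: √(0.5/83 + 0.5/166) = 0.095
- Ratio to the HS-only SE: √1.5 = 1.22, whatever the residual SD

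Clustering by class would widen these further.

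**The case against.** The article never says that the baseline regression answers question 4. It labels the outcome as baseline level, and describing correlates of starting skill is a legitimate aim. That stands, and it is why the regression can stay as description. It does not supply the missing analysis, and nothing else in the Results section does so for family or environment factors.

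Several stronger readings are tempting, and the text does not support them.

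- *The individual-factor analysis uses raw gains within HS and so cannot answer its question.* The article says only that gains are compared. It states neither that they are unadjusted nor that the comparison is confined to HS. Compared across groups, gains by factor can address modification, and the time x group x gender ANOVA already allows that contrast for gender. Even within HS, the comparison answers question 3 descriptively, since objectives 2 and 3 and question 3 are framed within groups.
- *The second aim has no valid analysis at all.* The Theoretical framework section counts the individual level among social-ecological factors, so the aim is partly covered.
- *Mediation is wrong for every personal factor.* Perceived motor competence is listed among the personal factors under Covariate and mediator, and Study procedure has it tested before and after. It remains a possible mediator.
- *Baseline correlates will be reported as determinants of HS efficacy.* That is a risk of misreading. The article does not announce it.

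It is also fair to object that a factor x group term would not settle the matter. Each arm is a single kindergarten, so the term is equally factor x kindergarten.

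**Conclusion.** The point holds for the family and environment levels. As written, question 4, the second aim, the differential-effect hypothesis and the statement under Strengths and limitations have no matching analysis there, because the one stated regression has a pre-intervention outcome. This conclusion rests on the text and the order of measurement. The simulation only illustrates it, and its percentages depend on the assumed values.

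For individual factors the finding is limited to an unspecified contrast and loose wording in question 3. The main comparison of HS, OPE and FP is untouched, and the analyses concerned are exploratory. The plan should be corrected, but the point does not threaten the trial's primary results.

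**What to change.** 1. Make post-test FMS adjusted for baseline, or the gain, the outcome of the social-ecological regression. State which, since the two can differ when groups are not equivalent at baseline. Fit it across the three groups with factor x group terms and allowance for class.
2. Keep the baseline-FMS regression, labelled as a description of starting skill.
3. Use the same factor x group contrast for age, gender and temperament, so that modification is separated from growth common to all groups.
4. In research question 3, replace *mediated* with *moderated* for age, gender and temperament. Mediation may be kept for perceived motor competence.
5. Label these analyses exploratory, and state that factor x group is confounded with factor x kindergarten.

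The cost is a change of wording in the plan; the data are already due to be collected. Interaction estimates will be imprecise: the standard error is about 1.22 times that of an HS-only slope before clustering, with only four classes per arm (12/3) to estimate class variation.
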